**Trial protocol for ethics application**

| Synopsis |  |
| --- | --- |
| **Name of the Funding Source:** Youth Program of National Natural Science Foundation of China (No. 82004490) and the Innovation Platform Open Fund project of the Hunan Education Department (no.20K091) and the University of South China Clinical Research 4310 Program（no.20214310NHYCG04） | **Protocol Number:**  Version 2.0 |
| **Study Title:** Electroacupuncture treatment of primary dysmenorrhea: a randomized, participant-blinded, sham-controlled clinical trial | |
| **Short Title:** Electroacupuncture Treatment of Primary Dysmenorrhea | |
| **Planned Study Sites:** This study will be spearheaded by the First Affiliated Hospital, Hengyang Medical School, University of South China as the leading unit. The sub-centers are the First Affiliated Hospital of Hunan University of Chinese Medicine and the Affiliated Changsha Central Hospital, Hengyang Medical School, University of South China. The three hospitals are affiliated with universities. | |
| **Number of Participants:** A total of 336participants | |
| **Chief Investigator:**  [name] | |
| **Study Period:** December 2022 – December 2025 | |
| **Objectives:** Primary dysmenorrhea is common among women, with both psychological and physical effects. Electroacupuncture has been used as alternative therapy for primary dysmenorrhea, although with no (non-anecdotal) evidence of effectiveness. This multicenter, randomized, participant-blinded, sham electroacupuncture-controlled clinical study will observe the prophylactic and therapeutic effects of electroacupuncture in participants with primary dysmenorrhea at three Chinese hospitals. Moreover, by observing changes in serum and urine metabolites before and after electroacupuncture, we evaluated the putative mechanisms mediating the electroacupuncture effects on patients with primary dysmenorrhea while focusing on the metabolic pathway. | |
| **Study Design:** This study is a randomized, participant-blinded, sham-controlled clinical trial trial. | |
| **Study Criteria:**  Inclusion criteria  Eligible participants must meet all of the criteria below to be considered for this study:  (1) Diagnosed with PDMM according to the International Classification of Diseases criteria (ICD-10-I63; Code: 902)  (2) Aged 16–35 years.  (3) Regular menstrual cycles (defined as 28-day cycles ± 7 days) for 4–7 menstrual days.  (4) Detailed contact information provided, with no short-term migration and ability to attend follow-up visits.  (5) Received no treatments within the preceding month, including acupuncture, NSAIDs, anti-inflammatory drugs, and analgesics.  (6) Willing to cooperate with the treatment procedures, medical examination, and efficacy evaluations, and must agree to not participate in other clinical experiments during the study period.  (7) Provision of written informed consent prior to participation.  (8) VAS score (i.e., the primary study endpoint described above) for three consecutive menstrual cycles ≥ 4 cm.  Exclusion criteria  Participants were excluded for any one of the following:  (1) Diagnosis of secondary dysmenorrhea (i.e., dysmenorrhea caused by uterine fibroids, adenomyosis, endometriosis, pelvic inflammation, internal foreign bodies, ovarian lesions, or other organic lesions).  (2) Irregular menstrual periods  (3) History of thrombosis, embolism, cerebrovascular disease, coronary artery disease, or high risk for thrombosis.  (4) Mental illness or cognitive impairment preventing comprehension of scale evaluation content.  (5) History of complications, depression, or antidepressant medication use.  (6) Severe heart, lung, liver, kidney, blood, immune, or endocrine system diseases.  (7) Hematopoietic diseases, acquired immunodeficiency syndrome, tuberculosis, hepatitis, or miscellaneous infectious diseases (as differentiated from the specific infections defined above).  (8) Malignancy, history of malignancy, or malignancy findings.  (9) Pregnancy, planned pregnancy, or lactation within 1 year.  (10) History of jaundice or herpes during pregnancy.  (11) Participation in other clinical studies within 4 weeks before provision of informed consent.  (12) Use of any of the following drugs within 4 weeks before provision of informed consent: gonadotropin-releasing hormone analogues or testosterone derivatives, hormone preparations containing mainly progesterone or estrogen, estrogen antagonists or aromatase inhibitors, and ongoing treatment for other gynecological diseases.  (13) Metal allergy or severe needle phobia such that electroacupuncture treatment cannot be tolerated.  (14)Skin rupture from needle, scars, or cardiac pacemaker.  (15) Other lesions or conditions deemed inappropriate or too complicated according to the judgment of the researchers, such as frequently changing work environment or unstable living conditions, which easily cause loss to follow-up. | |
| **Sample Size:** Based on previousPDMM therapy intervention studies, n = 168 participants will be required per group (total n=336) for this study. | |

# **Research Scope, Aims, Themes, Questions and Methods**

**Aims or Questions**

The primary aim of our study is to add to the existing evidence base on the effects of EA treatment on PDMM symptomology. Furthermore, we aim to find a suitable alternative to pharmaceutical treatment in patients with PDMM to reduce reliance on non-steroidal anti-inflammatory drugs (NSAIDs).

**Benefit of exploring these research questions**

At present, the Western medicine approach to treating dysmenorrhea mainly includes non-steroidal drugs. More specifically, drugs commonly prescribed for this condition include ibuprofen and oral contraceptives. However, the failure rate of these drugs is as high as 25% due to contraindications or intolerance. Moreover, these medications are associated with a high risk of adverse side effects. The long-term use of such drugs can cause liver, kidney, and digestive system disorders; inhibit ovulation; thin the endometrium; cause a series of adverse reproductive reactions (including impacts on menstrual volume), headache, and drowsiness; and even increase breast cancer risk.

In contrast, according to a recent meta-analysis, the effect of electroacupuncture (EA) on controlling PDMM symptomology was statistically significant in both animal experiments and clinical epidemiologic investigations . Moreover, EA serves as a safe and effective “green” therapy and therefore may be an excellent candidate as an alternative therapy within Western medicine.

**Outline the design of this research; its methods and details of the instruments to be used to collect the data, including psychometric properties if applicable.**

**Study design:**

We propose to conduct a multicenter, randomized, participant-blinded, sham-controlled clinical trial evaluating the effects of EA on PDMM in which participants will be publicly recruited. All centers must screen cases in strict accordance with the specified diagnostic, inclusion, and exclusion criteria, as specified below. A total of 336 participants with PDMM will be randomly assigned to two groups. The treatment group (n = 168) will receive EA, and the control group will receive SA (n = 168). The study will include the participants, implementing efficacy evaluators, and a data statistician. With regard to SA, the enrolled participants will be blinded and evaluated blindly after the last treatment.

**Study type:**

Interventional study

**Intervention and exposure:**

Intervention group:

EA group

Hwato brand disposable acupuncture needles (size 0.30 ×40 mm), and SDZ-V （Suzhou Medical Device Co., Ltd）electroacupuncture apparatuses will be used. Participants in the EA group will be treated at the following acupoints: bilateral sanyinjiao (SP6), located in the medial calf, 3 cun (approximately 60 mm) above the tip of the medial malleolus (Fig 2A) behind the medial edge of the tibia; and guanyuan (CV4), located in the lower abdomen on the anterior midline, 3 cun below the umbilicus (Fig 2B). The acupoints will be routinely disinfected prior to treatment. Acupuncture needles will be inserted 0.8–1.5 cun (approximately 16–30 mm) into the skin. Needle insertion will follow an angle of 30–45° in an inferomedial direction for SP6.

Fig2. The point positioning diagram

The acupuncture needle will be inserted vertically into CV4. Following needle insertion, small, equal manipulations of twirling, lifting, and thrusting will be performed on all needles to reach de qi (a composite of sensations including soreness, numbness, distention, heaviness, and other sensations believed to be an essential component for acupuncture efficacy). After de qi is achieved, paired electrodes on the electric needle device will be connected to the needle handle on one side of SP6 and CV4. Electroacupuncture stimulation will last for 30 min a priori, with a continuous wave of 100 Hz, and current intensities of 1–5 mA (the skin around the acupoints shakes slightly, which participants can typically tolerate without pain). We will administer EA seven days before each menstrual cycle until menstruation is over. Each menstrual cycle equals one course of treatment. We will evaluate a total of three courses of treatment (i.e., three menstrual cycles) in the current study. A total of 21 treatments will be performed. During treatment, operators (i.e., operating personnel) will be separated from follow-up personnel. We will also control for other influencing factors to avoid information bias.

SA group

Participants in the sham acupuncture group will receive sham electric acupuncture with false (sham) acupuncture points. The sham SP6 point is located 2 cun (approximately 40 mm) above taixi (KD3, midway between the spleen and kidney meridians [Fig 2A]). The sham CV4 point is located between the qihai (CV6) and yinjiao (CV7) levels, 3 cun lateral to the midline (Fig 2B). SA acupuncture needles will be inserted into the surface of skin (2–3 mm). There was no acupuncture technique whatever and have no de qi. The same electrode placements and other treatment settings will be used as in the EA group. However, the internal power cord will be cut off without any actual current output. Throughout the trial, participants will be treated individually with procedures in place to prevent communication between participants. To test for the blinding effect of the participants, all participants will be asked to guess whether they received an EA or a SA within 5 minutes of one session at week 12.

**How the planned methods achieve the aim or research questions**

**Primary outcomes:**

Participants will have been diagnosed with PDMM according to the criteria specified in the International Classification of Diseases criteria (ICD-10-I63; Code: 902) [10]. Moreover, VAS scores will be recorded before and after treatment (i.e., during the follow-up period). We adopted a methodology based on the VAS card created by the Pain Society of the Chinese Medical Association, ranging from “no pain” (at 0 cm on the left side of the scale card) to “the most severe pain” (at 10 cm on the right side of the scale card). The distance from the starting point of the scale to the patient evaluation measurement is recorded in cm. The VAS score is measured by the patient placing the cursor at the area best representing their subjective level of pain at the time of evaluation. The score is recorded according to the position of the cursor

**Secondary outcomes:**

Pain level on this scale is indicated by 11 numbers ranging from 0 to 10 (0 = painless, 10 = the most painful). The degree classification standard was scored as follows: 0 = painless, 1 to 3 = mild pain, 4 to 6 = moderate pain, 7 to 10 = severe pain. The participants will be scored according to their individual pain sensations. This method is easily understood by patients and can be either dictated or written. The CMSS is a total frequency score indicating an average severity evaluation of menstrual dysmenorrhea and includes information on specific symptoms of menstrual dysmenorrhea. Moreover, the traditional Chinese medicine symptom Score is formulated to score the evaluation of Chinese medicine symptoms according to the Guiding Principles for Clinical Research published by the Chinese Medical Science and Technology Press. The Self-Rating Anxiety Scale, Self-Rating Depression Scale, and 36-Item Short Form Survey are scales used to evaluate participants' mood and quality of life during treatment and follow-up. A metabolomics test on blood and urine samples is to be used to evaluate metabolic product changes occurring after the treatment of PDMM with EA and to provide findings informing the evidence base about putative mechanisms associated with metabolic pathways affected by EA.

**Statistical analysis:**

Descriptive statistics

We will perform statistical analyses using SPSS statistical software (version 26.0, IBM Corp., Armonk, NY, USA). A mixed-effect model will be used to compare change values before and after treatment for continuous variables. This analysis model divides the baseline scores as study covariates, accounting for grouping and central effects. Based on this model and differences before and after treatment, we will calculate the least squares mean of the two groups and the associated 95% credible interval of the difference between the two groups. Fisher's exact parametric method and nonparametric Kruskal Wallis tests will be used to evaluate dichotomous variables. Report exact p-values for all values greater than or equal to 0.001.A two-sided P-value of < 0.05 is considered the threshold for statistical significance.

Metabolomics analysis

We will perform first signal denoising, baseline and phase correction for all spec graphs, piecewise data integration, row and column normalization, and scaling normalization to conduct the metabolomics analysis. All data are to be processed using MestReNova software (Mestrelab Research, Santiago de Compostela, Spain). Pattern recognition analysis includes adopting the principal component analysis method of unsupervised mode recognition as well as a classification analysis (SIMCA), a partial least squares method, and a neural network method. All of these procedures will be conducted using SIMCA-P software (version 14. 0, Umetrics AB, Umea, Sweden). Pearson correlation analysis will be used to analyze characteristic hematuria metabolites as well as to determine the metabolites specific to PDMM and their associated metabolic pathways.

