**How will formal recruitment of potential participants be conducted?**

This study will use a PROC PLAN software environment (SAS version 9.4, SAS Institute Inc., Cary, NC, USA) for stochastic randomization. A third party produced a confidential dynamic randomization scheme using the Interactive Web Randomization System (Beijing LNKMED Tech Co., Ltd., Beijing, China, http://www.lnkmed.com/edc/a/sysIndex). The group assigned to each participant will be determined by a randomized file. Files will be randomly generated according to statistical units (SAS blocks). When the appropriate district length is selected, a random number of 336 participants will be generated for each of the three centers at a 1:1 ratio (this number shall not be reused) and will include the treatment assignments with corresponding serial numbers: 1001-1336, 2001-23316-336, and 3001-3336 (i. e., random coding table). After screening each eligible participants., the researchers at each center who did not participate in the treatment or evaluation were asked by the research assistant (non-blind personnel) to log into the randomized system and issue the center number randomly according to the enrollment order of the participants . For participants who complete the composition work although do not receive treatment, the random number cannot be reassigned to another participant. The next enrolled participant will receive the next random number in order. To ensure that each participant will receive the same chance of trial conditions in this randomized controlled study, we will balance the influence of confounding factors, avoid trial bias caused by subjective and random arrangements, and provide a scientific basis for statistical analysis. Participants from the three centers who are eligible for enrollment will be randomly assigned to receive an electric or sham needle using a 1:1 ratio. The present study design has been demonstrated as the most effective method for avoiding selection bias. Specifically, after allocation within the LNKMED Interactive Web Randomization System by a research assistant who will not be participating in the treatment and evaluation procedures, basic patient information will be entered into the allocation system to enroll patients meeting the inclusion criteria into the randomization process and obtain the corresponding randomization numbers and groupings. After enrollment, the clinical researcher will record the demographic information, including age, race, marital status, education level, employment status, comorbidities, and body mass index, within the study data system. Moreover, the duration of dysmenorrhea, treatment history, and related scale scores will be recorded before treatment. The study protocol includes regular monitoring and bias evaluations among centers.

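### Minor: randomisation is 1:1 within each centre and the continuous-outcome model keeps centre, but the tests named for dichotomous variables pool the three centres

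*Protocol*

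**What the plan says.** On allocation, the Protocol section on formal recruitment states that "a random number of 336 participants will be generated for each of the three centers at a 1:1 ratio", with a separate serial range for each centre. Staff then "issue the center number randomly according to the enrollment order of the participants". Centre is therefore a stratum of the randomisation. The same section also calls the scheme dynamic ("A third party produced a confidential dynamic randomization scheme using the Interactive Web Randomization System"), which should be reconciled with fixed lists, but centre remains the unit within which numbers are issued.

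On analysis, the first Statistical analysis section (Descriptive statistics) treats the two data types differently. For continuous variables, "This analysis model divides the baseline scores as study covariates, accounting for grouping and central effects". For binary variables, "Fisher's exact parametric method and nonparametric Kruskal Wallis tests will be used to evaluate dichotomous variables", with no mention of centre.

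The binary data that the Protocol foresees are not efficacy endpoints. They are adverse events and completion, listed in the later Statistical analysis section, and the week-12 treatment guess in the description of the sham group, where "all participants will be asked to guess whether they received an EA or a SA".

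**The concern.** When allocation is balanced within centres, differences between centres do not contribute to the difference between arms. A pooled 2×2 table nevertheless counts that between-centre variation in its variance. The test is then more cautious than its nominal level, and it loses power in proportion to how far the centres' event rates differ. Operators, recording habits and patient populations could all make such rates differ.

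The Protocol recognises this for continuous variables and drops it for binary ones without giving a reason. What is at stake is some sensitivity in any between-arm comparison of participants with an adverse event, of completion, or of the treatment guess.

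**Working it through.** **Inputs.** From the Protocol: 168 per group (336 in total), three centres, 1:1 within centre, two-sided 0.05. Not in the Protocol, and therefore assumed: 56 per arm in each centre (168/3), the control event rates by centre, and a common odds ratio (OR). The Protocol gives no event rate, effect size or power for any binary variable, so it has no figure of its own to reproduce here.

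**Why pooling costs power.** With centre rates p_k and equal centres, the pooled test uses the variance p̄(1−p̄), whereas the variance within centres is the mean of p_k(1−p_k).

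- 5/15/30%: pooled 0.1667×0.8333 = 0.1389; within (0.0475+0.1275+0.2100)/3 = 0.1283; ratio 0.92.
- 5/20/50%: pooled 0.25×0.75 = 0.1875; within (0.0475+0.1600+0.2500)/3 = 0.1525; ratio 0.81.
- 30/40/50%: pooled 0.2400; within (0.21+0.24+0.25)/3 = 0.2333; ratio 0.97.
- 2/5/10%: pooled 0.0567×0.9433 = 0.0535; within (0.0196+0.0475+0.0900)/3 = 0.0524; ratio 0.98.

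The pooled variance is clearly too large only when the centres differ widely.

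**Simulation.** Three tests were applied to the same simulated trials: Fisher on the pooled table, and the Cochran-Mantel-Haenszel (CMH) test over the three centres with and without continuity correction. With A the events in the EA arm, m_k the events in centre k and n = 56, CMH uses E = Σ m_k/2 and V = Σ m_k(112−m_k)/(4×111). It rejects when (|A−E|−0.5)/√V > 1.96; the uncorrected version omits the 0.5. Fisher is itself conservative because it is exact, so the corrected CMH is the like-for-like comparator.

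Scenarios with an OR of 1.9 used 200,000 trials, the others 40,000. The Monte Carlo standard error is at most √(0.25/40,000) = 0.25 points.

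Power, %:

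| Control rates by centre | Effect | Fisher | CMH corrected | CMH uncorrected | Like-for-like loss (points) |
|---|---|---|---|---|---|
| 10/10/10% | log OR 0.8 | 67.4 | 66.6 | 72.3 | none |
| 30/40/50% | OR 1.9 | 79.8 | 79.8 | 82.8 | 0 |
| 20/40/60% | OR 1.9 | 72.6 | 75.0 | 78.5 | 2.4 |
| 5/15/30% | log OR 0.7 | 62.0 | 65.8 | 70.8 | 3.8 |
| 5/20/50% | log OR 0.65 | 53.7 | 62.9 | 68.0 | 9.2 |
| 10/40/70% | OR 1.9 | 55.7 | 66.2 | 70.8 | 10.5 |
| 2/5/10% | OR 1.9 | 24.8 | 25.6 | 33.0 | 0.8 |

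Type I error, in the order Fisher, CMH corrected, CMH uncorrected: 2.9%, 3.4%, 5.1% at 5/15/30%; 2.0%, 3.5%, 4.9% at 5/20/50%; 1.8%, 3.7%, 5.0% at 10/40/70%. The pooled Fisher test is never above 5%.

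**Separating the two effects.** At 5/15/30% the full gap to uncorrected CMH is 70.8−62.0 = 8.8 points, of which 3.8 come from ignoring centre and 5.0 from Fisher's conservatism. At 5/20/50% it is 14.3 points, split 9.2 and 5.1. At 10% everywhere it is 4.9 points, none of it due to centre.

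Comparing two uncorrected tests (pooled Pearson against CMH) gives the same picture: 67.5 against 70.8, 58.7 against 68.0, and 72.3 against 72.3.

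**Check of the simulation.** For 40% against 55.9% with 168 per arm, the closed-form normal approximation gives 83.4% power. The simulated pooled tests give 84.6% (Pearson) and 81.9% (Fisher), which bracket it.

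**The case against.** Four things can be said in favour of the plan.

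- **Nothing important depends on these tests.** The primary outcome is VAS and the secondary outcomes are scale scores and metabolomics. All can use the model that already includes centre. This stands, and it limits the point to a minor one.
- **The listed uses are partly inferred.** For adverse events and completion the later Statistical analysis section only says that rates are calculated, and no test is named for the treatment guess. This also stands. The point bears on whatever between-arm binary comparisons are made, not on a specified test of those items.
- **The detail belongs in an analysis plan.** This holds only in part. The Protocol does not leave the method open: it names the tests for dichotomous variables and treats centre differently from the continuous case. Reporting of an estimate and interval is a different matter, since naming a test does not rule it out; that part is a useful addition, not a fault.
- **The spread in rates is hypothetical.** Correct. Nothing in the Protocol suggests rates as far apart as 5% and 50%, and with similar rates the loss is nil.

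Two stronger readings are tempting. A reader might infer that the whole 9 or 14 points of power is lost by ignoring centre, but roughly 5 points in each case is Fisher's exactness. A reader might also infer a safety problem, namely that a real excess of adverse events would go undetected. The documents do not support that. No between-arm test of adverse events is specified, and for rare events stratification changes power by under 1 point at 2/5/10% with an OR of 1.9. In other rare-event runs the gain was 0 points at 2/3/5% (43.4% for both tests), 1.1 at 3/6/12% (50.1 against 49.0) and 1.4 at 2/5/10% with higher power (54.1 against 52.7). An exact stratified test, which sparse tables need, would not recover the uncorrected-CMH gains either.

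**Conclusion.** The inconsistency is real and small. Centre is a stratum of the allocation and is kept for continuous outcomes, but the tests named for binary variables ignore it. The pooled Fisher test is valid and its type I error is not inflated; it is only needlessly conservative when centres differ.

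Like for like, the cost is about 0 points of power at equal or similar rates, about 4 at 5/15/30%, about 9 at 5/20/50%, and under 1 for rare events at an OR of 1.9. These sizes rest on assumed centre rates, a common odds ratio and equal centres of 56 per arm. The VAS analysis and the validity of the trial are unaffected.

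**What to change.** In the first Statistical analysis section (Descriptive statistics), replace the sentence on dichotomous variables. State that binary variables are compared between arms with a Cochran-Mantel-Haenszel test stratified by centre, in its exact stratified version where tables are sparse, and that the Mantel-Haenszel risk difference is reported with its 95% confidence interval. When making that edit, reconcile the word dynamic in the recruitment section with the fixed lists per centre, so that the stratification factor is unambiguous.

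The cost is one sentence and no new data, since centre is recorded for every participant. Little or no power is lost if the centres turn out alike: at 10% everywhere, corrected CMH gives 66.6% against 67.4% for Fisher. The only practical burden is running the exact version when counts are small.

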**Inclusion criteria**

Eligible participants must meet all of the criteria below to be considered for this study:

1. Diagnosed with PDMM according to the International Classification of Diseases criteria (ICD-10-I63; Code: 902)

(2) Aged 16–35 years.

(3) Regular menstrual cycles (defined as 28-day cycles ± 7 days) for 4–7 menstrual days.

(4) Detailed contact information provided, with no short-term migration and ability to attend follow-up visits.

(5) Received no treatments within the preceding month, including acupuncture, NSAIDs, anti-inflammatory drugs, and analgesics.

(6) Willing to cooperate with the treatment procedures, medical examination, and efficacy evaluations, and must agree to not participate in other clinical experiments during the study period.

(7) Provision of written informed consent prior to participation.

(8) VAS score (i.e., the primary study endpoint described above) for three consecutive menstrual cycles ≥ 4 cm.

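### The metabolomics analysis claims metabolites specific to primary dysmenorrhea although no one without it is studied, and it does not name the randomised EA-versus-SA contrast for the mechanism aim

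*Protocol*

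**What the plan says.** The last sentence of Metabolomics analysis (Protocol, first Statistical analysis section) applies Pearson correlation to blood and urine metabolites "to determine the metabolites specific to PDMM and their associated metabolic pathways". Before it, the paragraph lists principal components, a classification analysis, partial least squares and a neural network. It does not say which classes these methods are to separate.

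The population is fixed elsewhere. Inclusion criterion 1 reads "Diagnosed with PDMM according to the International Classification of Diseases criteria", and Study design says "A total of 336 participants with PDMM will be randomly assigned to two groups", with 168 to EA and 168 to SA. No third group is described.

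The mechanism aim appears in two other places. The synopsis Objectives would evaluate mechanisms "by observing changes in serum and urine metabolites before and after electroacupuncture". Secondary outcomes says the metabolomics test is "evaluate metabolic product changes occurring after the treatment of PDMM with EA". Neither phrase mentions the sham arm.

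The Descriptive statistics part of the same Statistical analysis section gives a general mixed-effect model for change in continuous variables. Baseline is a covariate, group and centre are accounted for, and the difference between the two groups is estimated.

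**The concern.** Specificity to a disease is a statement about people with the disease compared with people without it. A trial that enrols only people with the disease holds no information on that comparison. If the sentence stays, the report may present metabolites and pathways as markers of PDMM when the data cannot distinguish them from metabolites found in women generally.

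The wording of the mechanism aim raises a related risk. Read literally, it invites a before-after comparison in women given EA. Such a comparison cannot separate an effect of EA from anything that changes metabolites in both arms. PICOs makes the metabolomic mechanism part of the trial's secondary purpose, so this is a stated objective and not an incidental extra.

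**Working it through.** No figure in the protocol depends on this point, so there is none to reproduce. The only stated total, 336 = 2 × 168, is consistent.

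**1. Disease specificity**

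Inputs: 336 participants (Study design); PDMM required of each (Inclusion criteria, item 1); non-PDMM participants described: 0.

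Let D be disease status (1 = PDMM, 0 = not) and M a metabolite level. Specificity concerns mean(M | D = 1) − mean(M | D = 0). The second term has 0 observations, so the difference cannot be estimated. The same follows from the correlation formula r(M, D) = cov(M, D) / [SD(M) × SD(D)]. With D = 1 for everyone, cov(M, D) = 0 and SD(D) = 0, so r is 0/0 and undefined. A larger sample does not change this.

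Any Pearson correlation that can be computed must therefore be with something that varies within PDMM, such as the visual analogue scale (VAS) score, a symptom score or a change in one of them. That answers a different question, and it can mislead in both directions:

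- A metabolite that tracks pain severity may do so in any painful condition. It would correlate without being specific to PDMM.
- A metabolite altered equally in all women with PDMM would show no correlation with severity. It would be missed although it characterises the disease.

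**2. The EA effect on metabolites**

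| Place in the protocol | Contrast expressed |
| --- | --- |
| Synopsis, Objectives | before and after EA |
| Secondary outcomes | change after treatment with EA |
| Statistical analysis, Metabolomics analysis | none named |
| Statistical analysis, Descriptive statistics | EA versus SA difference in change, continuous variables |

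Only the last row gives a randomised comparison, and the metabolomics paragraph does not refer to it.

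An illustration shows why the choice matters. Assume that EA has no effect on a metabolite, that both arms shift by c standard deviations of change for other reasons, and that all 168 women in the EA arm are sampled. The protocol gives no value for c, so a range is shown. A two-sided 5% z-test of before-after change in the EA arm alone rejects with probability

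Φ(c√168 − 1.96) + Φ(−c√168 − 1.96), where √168 = 12.96.

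| c (assumed) | c√168 | Before-after test, EA arm only | EA-versus-SA test of change |
| --- | --- | --- | --- |
| 0 | 0 | 5% | 5% |
| 0.1 | 1.30 | 25% | 5% |
| 0.2 | 2.59 | 74% | 5% |
| 0.3 | 3.89 | 97% | 5% |
| 0.5 | 6.48 | about 100% | 5% |

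The between-arm test stays at 5% because the common shift cancels. The table shows what the literal before-after wording would risk. The protocol does not state that an EA-only test will be run.

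**The case against.** On specificity, the best defence is that the phrase is loose language for metabolites relevant to the condition. If so, rewording costs nothing. If it is meant literally, no statistical analysis plan can supply the missing comparator.

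On the EA effect, the other side is much stronger. A reader might infer that the mechanism claim is as unsupportable as the specificity claim. The documents do not bear that out:

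- A randomised sham arm exists, and nothing limits sampling to the EA arm.
- Metabolite levels are continuous and metabolomics is listed under Secondary outcomes, so the general mixed model can be read to cover them.
- The synopsis and Secondary outcomes phrases state purposes. Primary outcomes describes VAS recording in similar before-and-after terms, yet the general model compares change between groups.
- Details of the contrast may properly sit in an analysis plan that is not shown.

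What remains is narrower. The metabolomics paragraph sets out its own methods and software without pointing to the general model, and the two purpose statements mention EA only.

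Three further inferences also lack support. A count of chance findings would need an assumed number of signals and uncorrected signal-by-signal testing. The paragraph describes no such screen, and the later Statistical analysis section promises correction for multiple comparisons on all analysed outcomes, though without naming a method. A mismatch of menstrual phase between samples cannot be shown, because no sampling time is given. Regression to the mean is not shown for metabolites either, since women are selected on VAS and not on metabolite levels.

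**Conclusion.** The specificity claim is wrong as written. It rests on 0 of 336 participants without PDMM, and this conclusion needs no assumption beyond the absence of any described reference group or data.

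The EA mechanism claim is not ruled out by the design. It can be supported by an EA-versus-SA comparison of metabolite change, provided both arms are sampled. The fault there is wording: the aim is phrased as change around EA, and the metabolomics paragraph leaves the randomised contrast unnamed. The 74% to 97% rejection rates apply only if a before-after test in the EA arm were used, and only under an assumed common shift of 0.2 to 0.3 SD.

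The correction is worth making because it changes what the trial may conclude about a stated secondary purpose. It does not touch the VAS outcome or the sample size.

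**What to change.** In Metabolomics analysis, replace the claim of specificity with: *metabolites associated with symptom severity or its change among women with PDMM (exploratory)*.

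Add to the same paragraph: *Effects of EA on metabolites are judged by the EA-minus-SA difference in change from baseline, estimated with the general mixed model (baseline, group, centre) on serum and urine samples from both arms, with the multiplicity correction stated for all analysed outcomes.* Naming the model here also removes a doubt, because the later Statistical analysis section gives repeated measures ANOVA for secondary outcomes.

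Align the mechanism wording in the synopsis Objectives and in Secondary outcomes with this comparison.

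The cost is a narrower mechanism claim and slightly more analysis. No extra participants are needed, but samples from both arms are. If a disease-specificity claim is to be kept, a non-PDMM reference group would have to be added, which is a much larger change.
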